### Concealment mechanism {16b}

Each participant will receive a sealed, opaque envelope containing an assigned random number that determines their respective group assignment.

### Implementation {16c}

The envelopes will be unveiled by an independent researcher only after all participants have concluded the baseline assessments to avoid bias.

## Assignment of interventions: blinding

### Who will be blinded {17a}

It should be noted that complete blinding of both researchers and participants to the allocation of intervention targets is not feasible due to the inherent visibility of stimulation targets. Therefore, blinding will be selectively implemented, extending exclusively to the assessors and statisticians responsible for data collection and final statistical analyses.

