**Methods:**

This study employs a double-blind, sham-controlled, randomized controlled trial design with a 2-week intervention period. Both participants and outcome assessors will remain unaware of treatment allocation throughout the study. Thirty-nine stroke patients will be recruited and randomized into three distinct groups, including the sham tACS group (SS group), the single-target tACS group (ST group), and the multi-target tACS group (MT group), at a 1:1:1 ratio. The primary outcomes are series reaction time tests (SRTTs) combined with electroencephalograms (EEGs). The secondary outcomes include motor evoked potential (MEP), central motor conduction time (CMCT), short interval intracortical inhibition (SICI), intracortical facilitation (ICF), magnetic resonance imaging (MRI), Box and Block Test (BBT), and blood sample RNA sequencing. The tACS interventions for all three groups will be administered over a 2-week period, with outcome assessments conducted at baseline (T0) and 1 day (T1), 7 days (T2), and 14 days (T3) of the intervention phase.

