### Interventions

#### Explanation for the choice of comparators {6b}

The study included one sham and two active stimulation interventions delivered to three parallel groups.

In the SS group, a “pseudo stimulus” button will be discreetly activated, providing a semblance of stimulation to the subject without their awareness. For the ST group, the current channel will solely target M1, while the remaining three brain areas will receive pseudo stimulation, akin to the SS group. In the MT group, all four channels will be activated simultaneously. The entire process of electrical stimulation intervention will be closely supervised by a proficient clinical operator in conjunction with emergency personnel. Sham stimulation enables a placebo comparator to the active conditions.

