#### Intervention description {11a}

The multi-target tACS will be performed using a multichannel transcranial electrical stimulator (YingChi, Shenzhen). All participants will undergo a daily 20-min tACS session over a 2-week period. A skilled physiotherapist will conduct the sham tACS, single-target tACS, or multi-target tACS intervention on patients under the standardized condition. The tACS session will be delivered to the cortex via surface sponge electrodes (5 × 7 cm) soaked in 0.9% NaCl, which will be employed and secured in place using elastic gauze. Based on previous experimental research [29], the following stimulation parameters will be employed: a stimulating intensity of 1 mA peak to peak and a stimulation frequency of 40 Hz. For electrode placement, participants will receive a total of 4 pairs of electrode pads. The anodes will be placed in the M1, S1, DLPFC, and CB in alignment with the affected brain area, while cathodes will be placed in the contralateral brain area for each corresponding electrode [30].

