## Oversight and monitoring

### Composition of the coordinating center and trial steering committee {5d}

The principal investigators (PIs) of this clinical trial are PI # 1, [name], at the Shanghai Seventh People’s Hospital, Shanghai University of Traditional Chinese Medicine, and PI # 2, [name], at the Shanghai Seventh People’s Hospital, Shanghai University of Traditional Chinese Medicine. PI # 1 designs the concept of the research project including the stimulation protocol, the SSRT design, and all the neurophysiological recording methods. PI #1 also performs and analyzes along with her research team all neurophysiological recordings for all study participants of the clinical trial. PI # 2 leads the implementation of multi-target transcranial alternative current stimulation and regular rehabilitation training as well as the clinical assessments for study participants at the hospital. The trial steering committee is composed of the PIs and dedicated research staff.

The PIs and dedicated research staff will form the trial steering committee, which is accountable for coordinating and managing the whole project. Study governance for this single-site study is organized into the oversight team, recruitment team, intervention deployment and assessment team, neurophysiological recording and neuroimaging team, blood sample team, data management, and analysis team. The oversight team is led by the PIs and is responsible for global oversight of the conduct and progress of the study. Each team is led by a dedicated research staff or clinician. Each team works with the oversight team to develop and monitor standard operating procedures. Each team has a weekly meeting with the PI focused on decisions and progress within their scope of responsibility. Full study meetings are held quarterly and as needed.

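### The protocol calls the trial double-blind with participants unaware of their arm, but its blinding section restricts blinding to assessors and statisticians; masking of the EEG work is also not secured

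*Protocol article*

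**What the plan says.** The Abstract (Methods) sets the design label: "This study employs a double-blind, sham-controlled, randomized controlled trial design with a 2-week intervention period". It then says who is masked: "Both participants and outcome assessors will remain unaware of treatment allocation throughout the study".

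Section {6b} fits that claim. In the sham arm a pseudo-stimulus setting is used, "providing a semblance of stimulation to the subject without their awareness". In the single-target arm only the M1 channel is live, and the other three sites get the same pseudo stimulation as the sham arm. Section {11a} adds that "participants will receive a total of 4 pairs of electrode pads" and draws no distinction between arms.

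Section {17a}, which governs blinding, takes the other position: "complete blinding of both researchers and participants to the allocation of intervention targets is not feasible due to the inherent visibility of stimulation targets". It concludes that "blinding will be selectively implemented, extending exclusively to the assessors and statisticians responsible for data collection and final statistical analyses".

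On measurement and analysis, section {12} assigns assessments to physiotherapists who do not know the group, and section {20a} assigns the analysis to independent blinded statisticians. Section {5d} states: "PI #1 also performs and analyzes along with her research team all neurophysiological recordings for all study participants of the clinical trial". EEG recorded during the SRTT is part of the primary outcome.

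**The concern.** Whether participants know their arm is a basic property of a sham-controlled trial, and the protocol gives two incompatible answers. Staff cannot follow both.

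The primary behavioural outcome makes this matter. The SRTT asks patients for the fastest response they can give, so the result depends partly on effort and motivation. If operators take {17a} at its word and do not conceal the arm, patients on active stimulation may try harder or expect more than patients on sham. That difference enters the multi-target versus sham and single-target versus sham comparisons directly. The sham arm would then no longer serve as the placebo comparator that {6b} intends, and no later analysis could separate expectation from stimulation.

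The second, lesser issue is the EEG half of the primary outcome. Processing EEG involves judgement, so it matters whether those who record and process it are masked. The sections on this do not line up.

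**Working it through.** The protocol states no figure on this point, so there is nothing to recompute. The check is a comparison of the current text, section by section.

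| Section | Participants | Assessors | EEG/TMS recorders and analysts | Statisticians |
|---|---|---|---|---|
| Abstract, Methods | unaware | unaware | not mentioned | not mentioned |
| {6b} | sham intended to go unnoticed | – | – | – |
| {11a} | four electrode pairs, no difference by arm stated | – | – | – |
| {12} | – | blinded physiotherapists | not separately mentioned | – |
| {17a} | left out of blinding | blinded | covered only if counted as assessors | blinded |
| {20a} | – | – | – | independent and blinded |
| {5d} | – | – | one principal investigator and team; masking not stated | – |

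**Step 1: participants.** The Abstract includes participants among the masked. Section {17a} names two masked roles and uses a word of exclusion, so participants are outside the list. No other section reconciles the two.

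**Step 2: the reason given.** Section {17a} relies on the targets being visible. Pad position reveals the arm only if pads differ by arm. Section {11a} gives participants four pairs without separating the arms. Section {6b} has pseudo stimulation at three sites in the single-target arm, which implies pads at those sites, and describes the sham arm in the same terms. On that description, seeing the pads would not tell a patient which channels are live. An identical layout in every arm is a reasonable inference, but the protocol does not state it.

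**Step 3: consequence.** Either {17a} is wrong and gives up masking that the described set-up could provide, or the Abstract is wrong and the sham does not conceal. The text does not say which.

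**Step 4: EEG.** Sections {12} and {20a} describe masked assessors and masked statisticians. Section {5d} gives recording and analysis of all neurophysiology to one principal investigator with a research team and is silent on masking. It also places delivery of the intervention and assessment in a single team. The plan therefore does not secure masking of the EEG component, although nothing in it shows that masking is broken.

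**The case against.** Three points can be made on the other side.

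First, {17a} speaks of complete blinding to the intervention targets. It might mean only that patients can see where the pads sit, while still not knowing which channels are active. That is a sensible intention, but the next sentence restricts blinding to assessors and statisticians and leaves no room for masked participants. Condensation for a journal does not explain the conflict either, because the article states both positions.

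Second, a reader might infer that participant masking will fail in practice. The documents do not support that. The sham in {6b} may well conceal the arm, so what is shown is a contradiction and a conditional risk. This objection stands.

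Third, a reader might infer that the principal investigator who designed the stimulation and handles the EEG knows the allocations. No section says so:

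- Designing a stimulation protocol does not reveal who received it.
- Section {5d} gives leadership of delivery to the other principal investigator.
- Section {16c} has an independent researcher open the envelopes.
- The weekly team meetings are with the PI, without saying which of the two, and allocation is not listed as a topic.
- The assessors in {17a}, described there as responsible for data collection, could include whoever records EEG.

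This objection also stands. The EEG part is a gap to close and does not demonstrate unmasking.

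**Conclusion.** The contradiction on participant blinding is real and must be resolved before the trial is described as double-blind. It rests on the wording of the Abstract and {17a} alone and needs no assumption. That the visibility argument is weak rests on one inference, that all arms wear the same four pairs.

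The bias is conditional on staff following {17a}. Its size cannot be given, because the documents contain no figure for an expectation effect on the SRTT. Setting an assumed effect against the sample-size input would add nothing reliable.

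The EEG part is secondary. Sections {12}, {20a} and {5d} leave it unclear whether those who record and process EEG are masked, and this would not carry the point by itself.

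**What to change.** Reconcile the Abstract, {6b}, {11a} and {17a} in one statement:

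- All arms wear the same four-pair set-up, with pseudo stimulation on every inactive channel, and participants are blinded by this means.
- Only the person who opens the envelopes and those who operate the stimulator know the arm. Operators take no part in outcome assessment.
- Section {17a} lists participants, assessors, EEG and TMS recorders and analysts, and statisticians as masked.
- Section {5d} states that EEG and TMS recorders and analysts are masked to arm and work on files under coded identifiers.

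If participants cannot in fact be masked, remove the double-blind label and the sentence on participants from the Abstract, and describe the trial as assessor- and analyst-blinded.

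The cost is mainly wording and file coding. One practical point needs checking. Section {11a} has a physiotherapist deliver stimulation, {12} has physiotherapists assess, and {5d} places both functions in one team, so different people must fill the two roles. Whether current staffing allows this is not stated. Asking participants at T3 which arm they think they were in would be a useful optional check on masking, but it does not resolve the contradiction.

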### Procedure for unblinding if needed {17b}

Unblinding of group division will occur in situations where the staff deem this necessary for participant safety, to address a technical issue related to the tACS device, or another unforeseen situation in which tACS status is critical for study conduct.

## Data collection and management

### Plans for assessment and collection of outcomes {18a}

The plans for the assessment and collection of outcome, baseline, and other trial data, including any related processes to promote data quality and a description of study instruments along with their reliability and validity, have been described in the “Outcomes {12}” section.

### Plans to promote participant retention and complete follow-up {18b}

Firstly, we will provide the participants with a detailed explanation of the trial, including possible benefits while they sign the informed consent form. Secondly, free examination reports such as fMRI will be provided to participants.

### Data management {19}

As tACS technique is a low-risk intervention which has no substantial safety issues, there will not be a data monitoring committee.

### Confidentiality {27}

All data will be identified and labeled only by subject ID numbers, which will be stored separately from the identifying information and from consent and assent forms.

### Plans for collection, laboratory evaluation, and storage of biological specimens for genetic or molecular analysis in this trial/future use {33}

After the blood samples of the subjects were obtained by professionals, they were thoroughly mixed with TRIzol and stored in a − 80 °C freezer at the central laboratory of Shanghai Seventh People’s Hospital.

## Statistical methods

### Statistical methods for primary and secondary outcomes {20a}

Statistical analysis will be performed using IBM SPSS Statistics 25 (http://www.spss.com.hk). Independent statisticians who remain blinded to the grouping will use an intention-to-treat (ITT) analysis approach to scrutinize the study results. In the case of missing data, the last observation value will be used for interpolation. Continuous variables conforming to a normal distribution will be described as the mean ± SD, while nonnormal distributions will be presented as medians, and the categorical variables will be described using frequency counts. The two-way variance with repeated measures will be performed for continuous variables that meet the assumptions of a normal distribution and homogeneity of variance, while the Wilcoxon test will be used if not. A chi-square test will be performed for categorical variables. The comparison between the three groups will use a two-tailed multivariate analysis of variance. When the *P* value was less than 0.05, the results were statistically significant. The post hoc comparisons will be performed by the Bonferroni correction for multiple comparisons if necessary.

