### Eligibility criteria {10}

#### Inclusion criteria

Age between 40 and 75 years, possessing normal or corrected-to-normal vision.Right-handedness, as indicated by a score greater than 40 points on the Edinburgh Handedness Scale [27].Experienced a single (first ever), unilateral stroke (ischemic or intracerebral hemorrhagic) within the timeframe of 2 weeks to 6 months from onset.Exhibiting clear consciousness and absence of mental disorders, with a score exceeding 23 points on the Mini-Mental State Examination (MMSE) [28].Demonstrating a willingness to cooperate in the research and providing voluntary consent by signing the informed consent form.Presenting an upper limb with a Brunnstrom scale grade ranging from III to V.

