### Sample size {14}

The sample size calculation was conducted using G*power software (v3.1.9.2). The effect size of this study was estimated from a study conducted by Jaberzadeh et al. who investigated the differential effects of unihemispheric concurrent dual-site and conventional tDCS on motor learning using SRTT [11], which was determined to be 0.526. According to a prior two-way analysis of variance (ANOVA) F test, with a power of 0.95 and an alpha (α) level of 0.05, an estimated 32 participants will be needed. Considering a 20% drop-out rate, the final sample size of each group will be 10, with a total of 39.

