### Methods in analysis to handle protocol non-adherence and any statistical methods to handle missing data {20c}

The intention-to-treat principle (ITT) will be used to analyze the data.

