### Adverse event reporting and harms {22}

Due to the tACS technique being a low-risk intervention, no adverse event reporting is anticipated. During the tACS intervention, a professional doctor will always accompany the entire process. If the participant experiences any discomfort, the intervention will be stopped and proper treatment will be provided by the professional.

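### Carrying the last observation forward is the only missing-data method, in a trial where change after drop-out is expected in every arm; it attenuates or biases the arm comparison

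*Protocol article*

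**What the plan says.** Under Statistical methods for primary and secondary outcomes {20a}, the protocol article has one sentence on missing values: "In the case of missing data, the last observation value will be used for interpolation". It applies to primary and secondary outcomes alike. The item meant for missing data, {20c}, adds only this: "The intention-to-treat principle (ITT) will be used to analyze the data". The item on additional analyses {20b} plans none. The main analysis is a repeated-measures ANOVA: "The two-way variance with repeated measures will be performed for continuous variables that meet the assumptions of a normal distribution and homogeneity of variance".

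Other sections bear on whether values stay still after the last visit:

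- The abstract places "outcome assessments conducted at baseline (T0) and 1 day (T1), 7 days (T2), and 14 days (T3) of the intervention phase".
- The inclusion criteria admit patients "within the timeframe of 2 weeks to 6 months from onset".
- Item {11d} lets usual hospital treatment carry on.
- Each session of the series reaction time task (SRTT) has 10 practice and 80 test trials.
- The sample size section works with a loss allowance: "Considering a 20% drop-out rate".
- The harms section says: "If the participant experiences any discomfort, the intervention will be stopped and proper treatment will be provided by the professional".

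**The concern.** Carrying the last value forward is a single imputation that treats the value at the last visit as the value at day 14. That is plausible only if nothing changes in between. Here change is the expected course in every arm: early recovery after stroke, ongoing rehabilitation, and repeated practice on a task chosen because it measures learning. A patient last seen on day 1 would enter the day 14 comparison with almost none of that change. For RNA sequencing, sampled only at baseline and after 2 weeks, every drop-out would be given a change of exactly zero.

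At stake is the primary comparison between arms. The rule would act on it directly, and no planned analysis would show by how much. The intention-to-treat principle does not require the rule: it settles who is analysed and in which arm, not what a missing value would have been.

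**Working it through.** **The plan's own figure.** 32 × 1.2 = 38.4, rounded up to the stated total of 39. At 1:1:1 this is 13 per arm. Twenty per cent of 39 is 7.8, so the plan itself allows for about 8 patients with missing later values, or 2 to 3 per arm.

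**Formula.** Let G be the gain by day 14 common to all arms, D the true extra gain in the active arm, dA and dS the drop-out shares in the active and sham arms, and c the share of the change already reached when a drop-out was last seen. Suppose drop-outs would otherwise have followed the same course as those who stay. The mean recorded changes are:

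- active: (G + D) × (1 − dA(1 − c))
- sham: G × (1 − dS(1 − c))

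The difference is

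D × (1 − dA(1 − c)) − G × (1 − c) × (dA − dS).

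The first term is attenuation, present whenever drop-outs miss part of the change. The second is a bias that appears when drop-out differs by arm; its sign depends on which arm loses more. The same algebra applies to multi-target against single-target stimulation.

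**Inputs.** Visit days (1, 7, 14) and the 20% come from the protocol. G = 0.6 SD, D = 0.6 SD (or 0), linear change and the unequal drop-out splits are assumptions. Linear change gives c = 1/14 for loss after T1 (1 − c = 0.929) and c = 7/14 for loss after T2 (1 − c = 0.5).

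| Drop-out active / sham | True difference | Recorded, loss after T1 | Recorded, loss after T2 |
|---|---|---|---|
| 20% / 20% | 0.60 | 0.6 × (1 − 0.2 × 0.929) = 0.49 | 0.6 × 0.90 = 0.54 |
| 30% / 10% | 0 | −0.6 × 0.929 × 0.2 = −0.11 | −0.6 × 0.5 × 0.2 = −0.06 |
| 30% / 10% | 0.60 | 0.43 − 0.11 = 0.32 | 0.51 − 0.06 = 0.45 |
| 10% / 30% | 0.60 | 0.544 + 0.111 = 0.66 | 0.57 + 0.06 = 0.63 |

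At equal 20% drop-out the loss is therefore 19% (after T1) or 10% (after T2) of the true difference.

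**Range over the assumed gain.** With G from 0.5 to 1 SD and c from 0.5 to 0, the bias term at 30% against 10% runs from 0.5 × 0.5 × 0.2 = 0.05 SD to 1 × 1 × 0.2 = 0.20 SD.

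**Simulation.** With 13 per arm, an assumed within-patient correlation of 0.6, 0.6 SD common gain, no true effect and loss after T1, equal 20% drop-out gives a mean estimated standard error of 0.359 against an empirical 0.363, and a type I error of 5.1%. At 10% against 30% the type I error is about 6%.

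**The case against.** The strongest reply is that the effect is modest at this size. A false difference of 0.11 SD is under one third of the contrast's standard error (0.11 / 0.36 = 0.31). Type I error stays at about 5% to 6% in the 10% against 30% case, and reaches only about 7% at 0% against 30%. Loss after T2 roughly halves the bias. The gains and the true effect are assumed. This stands, and it limits how strongly the point can be put.

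The reply also holds against three stronger readings that a reader might infer:

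- *Standard errors are too small because filled values count as real data.* In the simulation above the estimated and empirical standard errors agree closely, and type I error is near nominal at equal drop-out.
- *The rule always shrinks the effect.* It does not: heavier loss from sham can inflate it (0.66 for a true 0.60), and the two terms can cancel. For the same reason the rule cannot be defended as conservative.
- *Drop-out will differ by arm.* This is plausible, since the arms have zero, one or four active channels, stimulation is stopped for discomfort, and the blinding section says participants cannot be fully blinded. But the documents give no figure for it. All participants wear four electrode pairs, with sham stimulation on inactive channels. Stopping stimulation is not the same as ending assessment; the text does not say that visits stop, nor that they continue.

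What the reply does not answer is the attenuation, which needs no unequal drop-out and follows from the plan's own 20% allowance.

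**Conclusion.** The concern holds in this form. The plan fixes a single missing-data method whose assumption conflicts with the course it expects in every arm, and it plans nothing that would reveal the effect. With equal drop-out a true arm difference is attenuated: at 20%, by about 10% to 19%, depending on whether patients leave after T2 or T1. With unequal drop-out the comparison is biased in either direction. The percentage loss at equal drop-out rests on linear change and on drop-outs otherwise following the course of those who stay. The SD figures rest also on the assumed gains, and the unequal scenarios on assumed splits. The type I error consequence is small, so this is a point that should be fixed rather than one that would invalidate the trial.

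**What to change.** Delete the last-observation sentence in {20a} and replace it as follows:

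1. For outcomes with repeated post-baseline visits, analyse all observed values with a likelihood-based mixed model with group, visit and group-by-visit. Enter T0 as a covariate, or model it as an outcome so that patients with no post-baseline value are kept. Deleting the sentence alone is not enough, because a conventional repeated-measures ANOVA drops patients with incomplete rows.
2. For outcomes with one post-baseline measurement, such as RNA sequencing, use observed values with baseline adjustment.
3. State that planned assessments continue in patients whose stimulation is stopped. This leaves the stopping rule itself untouched.
4. Add one simple, prespecified sensitivity analysis for data not missing at random.

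Cost: items 1, 2 and 4 are changes of wording plus slightly more analysis work, and the mixed model is available in the named software. Item 3 affects trial conduct, so it needs agreement with the assessment team. The mixed model assumes that data are missing at random, which is why item 4 is needed.

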### Outcomes {12}

Assessments will be conducted by physiotherapists blinded to the group allocation at various designated time points, as outlined in Table 1. Additionally, a comprehensive questionnaire (administered during week 0) will capture baseline information, including age, gender, symptoms, disease severity, duration, prior treatment, and medication history, which will be recorded using a questionnaire. Additionally, any encountered side effects throughout the course of the study will be promptly documented and reported in real time.

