## Assignment of interventions: allocation

### Sequence generation {16a}

A total of 39 eligible participants will be assigned to three groups at a 1:1:1 ratio using stratified randomization with sex, age, and stroke severity as factors in this study. The stratified randomization will be achieved as follows: Firstly, participants will be divided into men and women two groups. Secondly, the two groups will be grouped by age (< 60 and ≥ 60). Lastly, the four groups will be grouped by Brunnstrom scale grade (III, IV, V), a total of 12 subgroups. Finally, all 12 groups will be regrouped into three new groups including the SS group, ST group, and MT group to minimize the bias of the final results. The random number will be generated by Microsoft Excel (https://www.microsoft.com) and will be overseen by an external statistician who is not directly involved in the study.

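### The planned analysis adjusts for neither the baseline value nor the stratification factors, which gives up some precision in a trial of 13 per arm

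*Protocol article*

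**What the plan says.** Section {20a} fixes the model for continuous outcomes: "The two-way variance with repeated measures will be performed for continuous variables", with a Wilcoxon test if the assumptions fail. It adds: "The comparison between the three groups will use a two-tailed multivariate analysis of variance". Neither sentence names a covariate, and section {20b} plans no additional analyses.

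The Abstract (Methods) sets the schedule: "outcome assessments conducted at baseline (T0) and 1 day (T1), 7 days (T2), and 14 days (T3) of the intervention phase".

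Section {16a} allocates patients "using stratified randomization with sex, age, and stroke severity as factors in this study", with age cut at 60 and Brunnstrom grade standing for severity: "Lastly, the four groups will be grouped by Brunnstrom scale grade (III, IV, V), a total of 12 subgroups". None of these factors reappears in the analysis. Section {8}, by contrast, describes the allocation as simple random.

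**The concern.** In a two-way group-by-time model on this schedule with no covariate, baseline can help only as a fourth level of time. Two consequences follow.

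- The group-by-time contrast compares groups on their departure from T0. It therefore carries the variance of a change score, which is larger than the variance after regressing on T0.
- The group main effect averages in a visit at which treatment cannot yet have acted.

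Separately, stratifying on sex, age and Brunnstrom grade makes sense if they are thought to matter for outcome. If they do, leaving them out of the model keeps their variance in the error term, and the standard errors are then larger than the design warrants.

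At stake is the power to separate multi-target from single-target stimulation, the trial's stated question, with few patients per arm. All the data needed are already collected.

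**Working it through.** **Inputs from the documents.** N = 39 at 1:1:1 (sections {8}, {16a}), so 39/3 = 13 per arm. Alpha 0.05 with Bonferroni post hoc ({20a}), taken as 0.05/3 for three pairs. Effect size 0.526 ({14}); its metric is not stated, and it is read here as Cohen's f.

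**Assumed, not in the documents.** The correlation ρ between T0 and a later visit (0.3 to 0.8); equal SD at all visits, set to 1; a pairwise difference of 0.8 SD.

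**The plan's own figure.** 32 × 1.2 = 38.4, rounded up to 39. The 32 can be reproduced by a repeated-measures between-factor F test at f = 0.526 with two groups, four measurements and ρ = 0.5 (power 0.954), or with three groups, two measurements and ρ = 0 (0.956). Section {14} states none of these settings. A fixed-effects ANOVA needs 49–50 patients (1 numerator df) or 59–60 (2 df). So no ρ can be carried over from the sample-size section.

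**Dilution of the group main effect.** With a constant effect δ at T1–T3 and none at T0, the four-visit mean difference is (0 + δ + δ + δ)/4 = 0.75δ, a 25% reduction. This matters only if the main effect is the treatment test.

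**Change versus adjustment at T3.** Change variance: 1 + 1 − 2ρ = 2(1−ρ). Variance with T0 as covariate: 1 − ρ². Ratio: (1−ρ)(1+ρ) / [2(1−ρ)] = (1+ρ)/2. Patients a change analysis needs to match 39 adjusted: 39 / [(1+ρ)/2].

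**Pairwise power.** Noncentral t with noncentrality 0.8/√(2v/13), two-sided 0.05/3. Error df are 36 for change, 35 with T0, and 31 with T0 plus four stratification df (39 − 3 − 5). Example at ρ = 0.5: change v = 1.00 gives 0.8/√(2.00/13) = 2.04; adjusted v = 0.75 gives 0.8/√(1.50/13) = 2.36.

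| ρ | Change v | Adjusted v | Ratio | N to match 39 | Power, change | Power, T0 covariate | Power, T0 + factors explaining nothing |
|---|---|---|---|---|---|---|---|
| 0.3 | 1.40 | 0.91 | 0.65 | 60 | 0.230 | 0.366 | 0.362 |
| 0.5 | 1.00 | 0.75 | 0.75 | 52 | 0.332 | 0.446 | 0.441 |
| 0.7 | 0.60 | 0.51 | 0.85 | 46 | 0.553 | 0.635 | 0.629 |
| 0.8 | 0.40 | 0.36 | 0.90 | 43 | 0.759 | 0.806 | 0.801 |

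**Three-group test at T3, f = 0.526**, noncentrality 39 × 0.526²/v, change versus adjusted: 0.66 v 0.85, 0.81 v 0.91, 0.96 v 0.98 and 0.996 v 0.998 at the same four values of ρ.

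**Stratification factors.** Sex 1, age group 1 and Brunnstrom grade 2 make 4 df; T0 makes 5. In the three-group test at an assumed f = 0.4 and ρ = 0.5, power is 0.70 with T0 alone. Adding the factors gives 0.69 if they explain nothing further, 0.74 if they explain 10% of the residual variance, and 0.79 if 20%. Fitting all 12 cells (11 df) gives 0.68, 0.73 and 0.78.

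**Limit of these figures.** They charge lost error df only and take the covariates as balanced across arms. For normally distributed covariates left to chance, the expected variance of a pairwise difference is multiplied by 1 + q/(36 − q − 1). For T0 alone (q = 1) this is 1 + 1/34 = 1.03, and the ratios above stay below 1. For five unbalanced terms it is 1 + 5/30 = 1.17, which would use up the gain at ρ = 0.7 (0.85 × 1.17 = 0.99) if the factors explained nothing. The small cost of the factors therefore depends on stratification actually being carried out.

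**The case against.** The strongest reply is that this is a condensed article, that covariate lists are commonly left to an analysis plan, and that {20a} does not forbid covariates. A repeated-measures ANOVA that includes baseline is also a valid test under randomisation. The validity part stands: the documents do not support a reading that the planned test is biased or invalid. The first part does not remove the point, because {20a} does not leave the model open. It chooses one, and the chosen model uses neither T0 nor the design factors as covariates.

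It is also fair that T0 as a level of time is an inference: {20a} does not list the levels, and Table 1 is not shown. If T0 were left out of the time factor, the stated model would make no use of baseline at all, so the recommendation would be the same. Likewise, the 25% dilution applies only to the group main effect, and {20a} assigns the three-group comparison to a MANOVA without saying which visits or variables enter it.

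Three stronger readings are tempting and are not supported:

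- *A much larger gain.* Setting adjusted T3 against unadjusted T3 gives a far bigger contrast (variance 0.51 against 1 at ρ = 0.7). No section plans a T3-only analysis; the fair comparator is change from T0.
- *Time since stroke as a needed covariate.* Section {12} has a questionnaire "capture baseline information, including age, gender, symptoms, disease severity, duration, prior treatment, and medication history", but nothing in the documents says that duration is prognostic. It is not part of this point.
- *Standard errors certainly inflated by omitting the factors.* That requires stratification to have taken place as in {16a}, which {8} contradicts, and the factors to be prognostic beyond T0, which is unknown.

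**Conclusion.** The point holds as a loss of efficiency. On the model as stated, T0 is most naturally a level of time and the stratification factors are ignored. Conditioning on T0 cuts the variance of the T3 difference by 35%, 25%, 15% or 10% relative to change from T0 at ρ of 0.3, 0.5, 0.7 or 0.8. For an assumed 0.8 SD pairwise difference at 0.05/3, the gain in power falls from about 14 points at ρ = 0.3 to about 5 at ρ = 0.8. In the three-group test at f = 0.526 it is 2 points or less from ρ = 0.7 upward, because power is already high.

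The direction for T0 holds at every ρ examined; the size depends on a correlation that the documents do not give. The case for the stratification factors is weaker: they cost under 1 point if balanced and not prognostic, and gain about 4 to 9 points if they explain 10–20% of the residual variance. The figures assume equal SDs and 13 per arm. Section {14} also states 10 per group against a total of 39, which needs correcting; the ratio (1+ρ)/2 does not depend on the number per arm.

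**What to change.** Before any unblinded look at the data, replace the covariate-free model in {20a} with a repeated-measures model that has T1–T3 as outcomes and the T0 value of the same outcome as covariate, plus sex, age group and Brunnstrom grade as main effects rather than 12 cells. Report adjusted MT–ST, MT–SS and ST–SS differences with 95% confidence intervals, and say which contrast is the treatment test and what the MANOVA is for.

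Reconcile {8} with {16a} on simple versus stratified randomisation. If allocation was in fact simple, the case for T0 is unchanged, but the three factors are then an ordinary choice of covariates and no longer follow from the design.

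The cost is about a sentence in the methods and 5 degrees of freedom. No new data are needed.
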